		**Study period**					
		**t**_**0**_	**t**_**1**_	**t**_**2**_	**t**_**3**_	**t**_**4**_	**t**_**5**_
**Outcome**	**Assessment tool**	**Baseline**	**Month 1**	**Month 3**	**Month 6**	**Month 9**	**Month 12**
Status tracheal cannula (primary)	Decannulated [Y/N] [Reasons/Checklist) Unblocking time/day [min.] Total duration	x	x	x	x	x	x
Status mechanical ventilation (primary)	Weaned [Y/N] Current weaning stage Total duration	x	x	x	x	x	x
Survival	Death [Y/N] Time to death after discharge		x	x	x	x	x
Medical devices (e.g. PEG tube)	Checklist	x	x	x	x	x	x
Specific neurological medication	Checklist	x	x	x	x	x	x
Global neurological outcome	Glasgow Outcome Scale Extended (GOS-E)	x	x	x	x	x	x
Neurological status: Level of consciousness Degree of paresis Spasticity Dysphagia	Coma Recovery Scale-Revised (CRS-R) Motricity Index (MI) Resistance to Passive Movement Scale (REPAS) Bogenhausener Dysphagie Score (BODS) Penetrations-Aspirations Skala (PAS)	x	x	x	x	x	x
Pain scale	Visual analogue scale (0 – 100)	x	x	x	x	x	x
Activities of daily life	Barthel-Index (BI)	x	x	x	x	x	x
Quality of life (QOL) (Patient and relatives)	European Quality of Life-5 Dimensions (EQ-5D-5L)	x	x	x	x	x	x
Social participation (Patient and relatives)	WHO Disability Assessment Schedule (WHODAS 2.0)	x					x
Depression/anxiety (Patient and relatives)	Hospital Anxiety and Depression Scale (HADS)	x	x	x	x	x	x
Burdens on the relatives (relatives)	Modified Caregiver Strain Index (MCSI)		x	x	x	x	x
Complications (including unplanned hospitalisations)	Semi-standardised free text	x	x	x	x	x	x
Satisfaction with health care situation (Patient, relatives, and home-based intensive care personnel)	10-point Likert scale		x	x	x	x	x
Adherence to the treatment pathway (IG)	[Y/N] Checklist Free text		x	x	x	x	x
Utilisation of healthcare (e.g. HSINC, hospital stays, outpatient medical services, aids)	Checklist AOK Bavaria data		x	x	x	x	x
Costs at the expense of SHI (separated according to sectors, cost types)	Costs per type in Euro [€] (AOK Bavaria)						x
Whereabouts of the patient	Checklist		x	x	x	x	x

*IG* Intervention group, *SHI* Statutory health insurance

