Defined changes of vital signs will trigger the HSICN staff to send the current patient's medical condition reports to the ROC. Based on these reports, the therapy plans and weaning protocols will be updated in interdisciplinary team conferences and will be forwarded to the home-based intensive care staff.

In addition, the intervention includes visits to study participants by outpatient follow-up teams consisting of physicians and therapists dispatched by the ROC. Each ROC has an outpatient follow-up team that covers its region. The visits will start 4 weeks after discharge from neurological early rehabilitation and will continue with visits every three months thereafter for one year. At each visit (t_1_-t_5_) the outpatient follow-up teams perform discipline-specific examinations, including blood gas analysis (BGA) and FEES. Additional visits to the HSICN by the ROC are possible, if needed.

Once the potential for weaning from mechanical ventilation and/or decannulation is considered by the outpatient follow-up team, the study participant will be admitted to the respective ROC. Here, a more comprehensive assessment of the potential for weaning from mechanical ventilation and/or decannulation is conducted as part of a structured diagnostic process over a few days (“Interdisciplinary Inpatient Structured Assessment”, IISA).

If the potential for successful weaning and/or decannulation is confirmed during an IISA, an inpatient neurorehabilitation program with a weaning procedure similar to NER will follow (“Neurological interval rehabilitation”, NIR).

In addition to the above-mentioned experimental intervention aspects the outpatient follow-up teams will document study data at each visit (t_1_-t_5_) (as specified in Table 2).

For compensation to those who suffer harm from the experimental intervention a liability insurance coverage has been established.

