#### Control condition

Participants in the control group will not receive trial-related healthcare interventions, but rather the conventional treatment, i.e. the standard healthcare as currently applied in the outpatient setting in Germany. In this setting, patients in the HSICN-setting are usually cared for by a general practitioner (and/or specialized physicians) and therapists as individually needed and prescribed. Aside from the specific experimental intervention (as described above) no concomitant care and interventions are prohibited in the control condition during the trial. The comparator was chosen since the research question is whether the introduction of the new healthcare practice affects outcome including cost-effectiveness; thus a comparison to “usual care” is warranted.

Participants in the control group do, however, also receive visits from the outpatient follow-up team at the same frequency as participants in the intervention group, but only for study data collection (compare Table 2).

All trial participants (experimental and control condition) will receive recommendations for post-trial care with their final visit Fig. 2.

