#### Monitoring and data management

Before recruitment begins, the study centres receive training on the study protocol, use of the assessment instruments, the study documentation, the forwarding of the study documentation to the evaluating institutions, as well as the process and obligations regarding data validation. Video-based and written training material is made available via an access-restricted web site for continuous training purposes. Individual training and delegation of study processes are documented by corresponding logs in investigator site files.

The monitoring is carried out by the central project co-ordination (LMU) and the evaluating institution (UMG) independently of both the funding agency and participating centres and will commence after the inclusion of the first patients, in order to ascertain compliance with the study protocol, and to identify problems and difficulties in the implementation and documentation at an early stage.

After enrolment, patients will receive an identification number as an encryption (pseudonymisation), so that their names will only appear on the informed consent form and a patient identification log, but not on other study documentation. The data collection is realized on the basis of CRFs (Case Report Forms).

The CRFs are forwarded digitally from the recruiting centres or ROC to password-protected cloud areas on servers of the University Medical Center Greifswald responsible for the independent clinical scientific evaluation. The original CRFs remain in the recruiting centres or ROC, respectively.

Subsequently, the evaluating institution will review all CRFs for missing entries, inconsistencies and implausibility, and resolve potential queries with the study teams of the participating centres. Thereafter, CRF-documented trial data will be entered in a digital database and double-checked for correctness.

The AOK Bavaria transmits the pseudonymised data of inpatient treatment to the University of Greifswald (UG) for the health economic evaluation. A trustee agency is responsible for providing a linking between the primary data of the study (as documented on CRFs) and the routine data of the AOK Bavaria.

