### Risk of bias considerations

The study design was chosen to ensure the best possible protection against systematic bias.

Potential selection bias is prevented by the concealed, stratified random allocation of patients to treatment groups in blocks by a partner not involved in recruitment.

No blinding of study personnel, patients or those conducting the evaluation will be possible for the experimental intervention, which increases the potential for performance bias and detection bias. Given the objective nature of the primary outcomes risk of detection bias is, however, considered low for these outcomes.

To reduce potential over- or underestimation of the intervention effect due to study dropouts (attrition bias), an intention-to-treat analysis will be conducted.

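### Satisfaction at t1–t5 is documented by the outreach team that delivers the intervention, so that comparison is at risk of differential courtesy bias

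*Protocol article*

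**What the plan says.** **What is measured.** Table 2 schedules "Satisfaction with health care situation (Patient, relatives, and home-based intensive care personnel") on a 10-point Likert scale at t1–t5, without a baseline. The Modified Caregiver Strain Index (MCSI) has the same schedule. HADS and EQ-5D-5L are taken at t0–t5, and WHODAS 2.0 only at t0 and t5.

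**Who provides the service.** Under Experimental condition, "the intervention includes visits to study participants by outpatient follow-up teams consisting of physicians and therapists dispatched by the ROC". The same section says: "Each ROC has an outpatient follow-up team that covers its region".

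**Who collects the data.** Again under Experimental condition, "the outpatient follow-up teams will document study data at each visit (t_1_-t_5_) (as specified in Table 2"). Under Control condition, controls "also receive visits from the outpatient follow-up team at the same frequency as participants in the intervention group, but only for study data collection". The Outcome assessment section attributes the assessments to trained study personnel and does not say that they are independent of the treating team. Baseline is taken by staff of the early rehabilitation hospital, before randomisation.

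**Who keeps the forms.** Monitoring and data management: digital copies go to the evaluation centre (UMG), and "The original CRFs remain in the recruiting centres or ROC, respectively".

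**What is said about bias.** The Risk of bias considerations section concedes that nobody can be blinded and that this raises performance and detection bias. It then adds: "Given the objective nature of the primary outcomes risk of detection bias is, however, considered low for these outcomes".

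**The concern.** The same visitor stands in a different relation to the respondent in each arm. In the intervention arm, the visitor belongs to the team whose service is part of the care being rated. The ROC issues the managed care plan and runs the advice line for the home nursing staff, and the follow-up team's view of the patient's potential leads to admission. In the control arm, the visitor has no part in care. People tend to be polite about a service when someone from that service records the answer. If that happens here, it happens in one arm only.

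All three groups that rate satisfaction are exposed: patients, relatives and home nursing staff. The Methods for additional analyses section plans between-group analyses of the secondary outcomes, and the Discussion says the trial will describe effects on emotional well-being and on caregiver burden. An arm difference in satisfaction could then not be cleanly separated from an effect of who asked the question.

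**Working it through.** **Step 1. Reading the sections side by side.**

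| Question | Intervention arm | Control arm |
|---|---|---|
| Who visits at t1–t5? | ROC follow-up team | ROC follow-up team |
| Does that team provide care? | Yes | No, data collection only |
| What does the satisfaction item cover? | Care situation including the ROC service | Care situation provided by others |
| Where do the original CRFs stay? | ROC, for the follow-up visits | ROC, for the follow-up visits |
| Does the low-risk argument apply to satisfaction? | No, primary outcomes only | No, primary outcomes only |

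Using one team for both arms equalises contact but not the relationship. The asymmetry is in the text as written.

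**Step 2. How direct the mechanism is, by instrument.** Satisfaction asks about care, so the mechanism is direct. MCSI, HADS, EQ-5D-5L and WHODAS ask about the respondent's own strain, mood, health or participation, so it is weaker. For WHODAS it can act only at t5. Satisfaction and MCSI have no baseline to adjust for.

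**Step 3. The plan's own sample size.** Inputs from the Sample size section: 30% v 10%, 2:1 allocation, 80% power, alpha 5% (two-sided reproduces the figure). Pooled proportion = (0.10 + 2 × 0.30)/3 = 0.2333.

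n(control) = [1.96 × √(1.5 × 0.2333 × 0.7667) + 0.8416 × √(0.10 × 0.90 + 0.30 × 0.70/2)]² / 0.20² = 48.1, rounded up to 49. This gives 49 + 98 = 147, and 147/0.85 = 172.9, so 173. The stated figures reproduce. They serve only to supply the 98 and 49 used below.

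**Step 4. What a reporting shift could do (assumed figures).** The documents give neither an SD for the satisfaction score nor the size of any shift. Assume no true effect, 98 v 49 raters and a two-sided 5% z-test at one time point.

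- SE = SD × √(1/98 + 1/49) = SD × 0.175. With SD 2, SE = 0.35.
- Probability of a significant result = Φ(shift/SE − 1.96) + Φ(−shift/SE − 1.96).
- Shift 0.5, SD 2: 0.5/0.35 = 1.43, giving 0.30.
- Shift 1, SD 2: 1/0.35 = 2.86, giving 0.82.

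| Assumed SD | Shift 0.5 point | Shift 1 point |
|---|---|---|
| 1.5 | 48% | 97% |
| 2.0 | 30% | 82% |
| 2.5 | 21% | 63% |

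**Step 5. Fewer raters.** Some patients will be unable to rate. If only half could (assumed, 49 v 25, SD 2), SE = 2 × √(1/49 + 1/25) = 0.49, and the two figures fall to about 17% and 53%.

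**The case against.** **Mode of completion is not stated.** A reader might infer that respondents cannot answer without their provider seeing it. The article does not say this. Forms might be read aloud, handed over or sealed, and an article may leave that detail to the full protocol. This stands. What the article does say is that the treating team documents the data and that the original CRFs stay at the ROC. If the full protocol already separates the two, the sponsor need only say so.

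**The limitation is already admitted.** The Risk of bias considerations section concedes detection bias in general and claims low risk only for the primary outcomes. This also stands: nothing there is misstated. But no protection is described for the self-reported outcomes, and they are to be compared between arms.

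**The team is not the sole object of the rating.** The item covers the whole care situation, including home nursing, general practitioner and therapists. This is fair, and it dilutes the mechanism for satisfaction without removing it.

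**Direction is not shown.** A reader might infer that satisfaction, strain, mood and quality of life all carry courtesy bias in favour of the intervention. The documents do not support that. Because the team's judgement can lead to admission, relatives might instead stress need or strain. Favourable bias is the likelier direction for satisfaction, but this is reasoned, not demonstrated.

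**Size is assumed.** This is correct. The calculation also models a single comparison, whereas the plan uses longitudinal models.

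**Removing the forms from the visits could lose data.** Satisfaction alone could produce up to 3 × 5 × 173 = 2,595 ratings, and home visits were chosen partly to keep follow-up complete. Reminders sent by UMG would sit badly with pseudonymised documentation. This rules out a postal scheme, but not sealing the form during the existing visit.

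**Conclusion.** The point holds as a risk, chiefly for satisfaction. As written, the team that delivers the intervention documents the ratings in both arms, is part of what is rated in only one of them, and belongs to the centre that keeps the original CRFs. The resulting bias would differ by arm and probably favour the intervention. For MCSI, HADS, EQ-5D-5L and, at t5 only, WHODAS, the risk is weaker.

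The size is unknown. Under the assumptions shown, a shift of 0.5 to 1 point with no true effect would produce a significant satisfaction difference in roughly 21–97% of trials with 98 v 49 raters, and in fewer if many patients cannot respond. These figures show that a modest shift would be enough to mislead. They do not estimate what will happen.

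Nothing here touches the primary outcome, the sample size or the power. The change is a cheap improvement to secondary outcomes, not a condition for the trial's validity.

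**What to change.** At the existing visits t1–t5:

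1. Relatives, home nursing staff and patients who are able complete the satisfaction form themselves, and preferably the MCSI and the other self-report forms too.
2. The respondent seals the form under the study pseudonym. The team forwards it unopened to UMG, and it is left out of the originals kept at the ROC.
3. Respondents in both arms are told that the ROC will not see the answers.
4. Where self-completion is not possible, the mode of completion is recorded, and comparisons that rest on such answers are reported as at risk of reporting bias.
5. The Risk of bias considerations section says expressly that its low-risk argument does not extend to the self-reported outcomes.

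**Cost.** Envelopes and an instruction in the CRF manual. No extra staff, visits or reminders are needed. There will be somewhat more missing or incomplete items, because the team cannot check the form on the spot. Enrolment began in March 2022, so a change now mixes two collection modes. The mode should be recorded for every form, and the change made on one date in all four regions and both arms. Open-label reporting bias remains, since respondents still know their arm.

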### Intervention

#### Experimental condition

The experimental condition is a new systematic healthcare bundle, primarily based on post-discharge specialized outpatient follow-ups by ROC-based neurorehabilitation teams for people with a need for ongoing mechanical ventilation and/or tracheal cannula and hence for HSICN after discharge from NER. The intervention will provide team-based neurorehabilitation healthcare counselling and support during the first year after discharge from NER that aim at promoting further functional neurological recovery with a focus on breathing and swallowing and consecutively continued weaning from mechanical ventilation and/or promoting a functional status that safely allows decannulation. Teams are physician-led and can include specialized breathing therapists trained to support weaning form mechanical ventilation, dysphagia therapists, physiotherapists, occupational therapists, and/or specialized nursing staff.

Elements of the healthcare bundle are:Team sessions in the ROC to evaluate participants’ data (see 2 & 3), develop and communicate a managed care plan with healthcare recommendations to the HSICN staff, treating physicians and therapists;Continuous exchange of vital data, mechanical ventilation and tracheal cannula management data, as well as laboratory data between the HSICN and the ROC; a telephone hotline is available to HSICN in case of need for advice regarding patient care;Regular patient visits within their HSICN-setting by the ROC-based outreach teams to assess participants’ clinical status personally including blood gas analysis, BGA, and functional swallowing assessment (fiberendoscopic evaluation of swallowing, FEES);Short inpatient re-evaluations in the ROC when a potential for weaning and/or decannulation is observed;Inpatient neurorehabilitation period (couple of weeks) in the ROC when the short inpatient re-evaluation indicated the likelihood of a successful weaning and/or decannulation.

Sequence of events:

As a central part of the experimental intervention, therapy plans for long-term weaning from mechanical ventilation and/or decannulation will be developed in collaboration with outpatient healthcare providers (e.g. general practitioners, physiotherapists, HSICN staff).

Defined changes of vital signs will trigger the HSICN staff to send the current patient's medical condition reports to the ROC. Based on these reports, the therapy plans and weaning protocols will be updated in interdisciplinary team conferences and will be forwarded to the home-based intensive care staff.

In addition, the intervention includes visits to study participants by outpatient follow-up teams consisting of physicians and therapists dispatched by the ROC. Each ROC has an outpatient follow-up team that covers its region. The visits will start 4 weeks after discharge from neurological early rehabilitation and will continue with visits every three months thereafter for one year. At each visit (t_1_-t_5_) the outpatient follow-up teams perform discipline-specific examinations, including blood gas analysis (BGA) and FEES. Additional visits to the HSICN by the ROC are possible, if needed.

Once the potential for weaning from mechanical ventilation and/or decannulation is considered by the outpatient follow-up team, the study participant will be admitted to the respective ROC. Here, a more comprehensive assessment of the potential for weaning from mechanical ventilation and/or decannulation is conducted as part of a structured diagnostic process over a few days (“Interdisciplinary Inpatient Structured Assessment”, IISA).

If the potential for successful weaning and/or decannulation is confirmed during an IISA, an inpatient neurorehabilitation program with a weaning procedure similar to NER will follow (“Neurological interval rehabilitation”, NIR).

In addition to the above-mentioned experimental intervention aspects the outpatient follow-up teams will document study data at each visit (t_1_-t_5_) (as specified in Table 2).

For compensation to those who suffer harm from the experimental intervention a liability insurance coverage has been established.

#### Control condition

Participants in the control group will not receive trial-related healthcare interventions, but rather the conventional treatment, i.e. the standard healthcare as currently applied in the outpatient setting in Germany. In this setting, patients in the HSICN-setting are usually cared for by a general practitioner (and/or specialized physicians) and therapists as individually needed and prescribed. Aside from the specific experimental intervention (as described above) no concomitant care and interventions are prohibited in the control condition during the trial. The comparator was chosen since the research question is whether the introduction of the new healthcare practice affects outcome including cost-effectiveness; thus a comparison to “usual care” is warranted.

Participants in the control group do, however, also receive visits from the outpatient follow-up team at the same frequency as participants in the intervention group, but only for study data collection (compare Table 2).

All trial participants (experimental and control condition) will receive recommendations for post-trial care with their final visit Fig. 2.

**Fig. 2 Fig2:**
[figure not shown]
Flow chart: Trial course of control and intervention group in the OptiNIV trial. Abbreviations: NR = Neurorehabilitation; FEES = fiberoptic endoscopic evaluation of swallowing; BGA = blood gas analysis

### Outcomes

Outcomes of the trial are specified in Table 2.

#### Primary outcomes

The primary outcome is defined as the rate of participants, who could be weaned from mechanical ventilation and/or decannulated one year after discharge in the intervention and control group, respectively.

#### Secondary outcomes

Secondary outcomes include the following: Tracheal cannula and ventilatory status and modalities, mortality, neurological status, activities of daily living, quality of life (QOL), depression/anxiety, pain, social participation, burden on the relatives, healthcare situation (use of home-based intensive care, living arrangement), satisfaction with healthcare situation, utilisation of healthcare (medical services, medication, remedies and aids, hospital care), complications/adverse events (including unplanned hospitalisation).

